## Statistical methods

### Comparison between VD model and CAU model

T, Chi-square and various kinds of regression tests will be used to compare DCR (binary variable), DCS (continuous variable), and hospitalization (continuous variable) and incidence of risky behavior (binary variable) rates between the VD and CAU models. Repeated analyses of variance will be used to compare psychiatric symptoms and social function (continuous variable) scores between the two groups.

We will use a difference-in-difference regression model with one treatment variable and additional regressors as control variables (see below). Insofar as perfect randomization and program execution are rarely achieved, we make use of an equation with a difference-in-difference Ordinary Least Square (OLS) estimator with additional regressors to estimate population true coefficients. The example below uses DCS as the dependent variable.

$$\begin{array}{l} \mathrm{\Delta DC}S_{i}=\beta_{0}+\beta_{1}\mathrm{VDmode}l_{i}+\beta_{2}{\text{SocialEconDemog}}_{i}\\ \;+\beta_{3}{\text{SeverityIllness}}_{i}+\beta_{4}{\text{FamilyCare}}_{i}+u_{i} \end{array}$$

∆DCS: This is the value of DCSi for the i^th^ individual at the end of the experiment minus the value of DCS_i_ at the start, or the change. DCS is the Drug Compliance Score, a continuous variable ranging from 0-10, with 0 indicating zero compliance and 10 full compliance.

Treatment (VDmodel): This is a binary variable indicating whether an individual is enrolled in the treatment model (VD) or the control group (CAU). Treatment = 1 if an individual is in the treatment group and 0 for individuals in the control.

Social EconDemog: This refers to social, economic and demographic characteristics that can be plugged into the model as additional control variables for analysis.

Illness Severity: This is a composite of variables relating to illness severity such as number of years an individual has been diagnosed with schizophrenia before the start of our program, and days of hospitalization due to schizophrenia over the two years before the start of the program.

β4FamilyCare i: This variable indicates the level of care an individual receives from his or her family.

u_i_: This is the residual of all other determinants of DCS.

In the above equation, β_1_ indicates program effect, *i.e*., the effectiveness of village doctors in managing villagers with schizophrenia as measured by the average change in DCS for those in the treatment group (VD) minus the average change in DCS for those in the control group (CAU).

There are several advantages to using this model. First, the coefficient in which we are most interested, β_1_, is more efficient than other estimators as it has a smaller variance or standard error than a simple difference estimator when unobserved determinants of DCS persist over time for a given individual. Second, this model eliminates possible pre-program differences in DCS between the treatment and control groups; for example, while using cluster randomization, we may not achieve true randomization at the individual level since it is possible (though unlikely) that all eligible individuals within a cluster could be assigned to a treatment or to a control group. Finally, the difference-in-difference equation allows for additional variables to be added to the treatment variable in the VD group. As these added regressors are possible determinants of the dependent variable DCS, including them improves the efficiency of the OLS estimator, β_1,_ which is the coefficient for program effect, thus addressing: potential bias introduced by imperfect randomization; partial compliance wherein patients with more severe illness in the VD group may at times elect not to comply with village doctors’ care, while patients with milder disease or more supportive family members in the CAU group may, of their own initiative, seek care from their village doctors; and attrition as severely ill patients are lost to follow-up (depending on the data collected, we will seek instrumental variables to address bias introduced by drop-outs). That said, we anticipate a high take-up rate by patients in rural Liuyang because the free antipsychotics program has been operating in the municipality for several years and has been well accepted by patients and their families. Given past experience in Liuyang, we anticipate a drop-out rate of 10% over the course of the study.

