## Methods

### Sampling and cluster randomized controlled design

We will conduct a cluster randomized controlled trial involving a sample of rural schizophrenia patients in Liuyang Municipality, Hunan Province, China. Criteria for the sample include:

1. Resided in one of the administrative rural villages of Liuyang Municipality for the past year.

2. Diagnosed by psychiatrist as having schizophrenia.

3. Registered for free medication under Project 686.

Due to our long time working relationship with the local government in Liuyang, they have agreed to assist us in the random selection of villages. A total of 40 administrative villages will be selected out of 318 administrative villages at random. We will use the statistical software package STATA to generate 40 random numbers. All villages will be randomized into two groups (the intervention arm and the control arm) by block sampling (block size = four). The randomization will be based on villages rather than individuals. Due to the nature of our experiment, the allocation will not be blinded for the service providers, patients and interviewers, but those who analyze the data will be blinded for the group information. The co-PI of this project, who is a statistician, will be responsible for the random allocation sequence and the assignment of clusters to interventions.

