### Sample size

To minimize contamination and simplify project management, we will use one-stage clustered sampling. For a two-sided significance level of 0.05 and power of 80%, the sample size is calculated for both the binary variable Drug Compliance (DC) and the continuous variable Drug Compliance Score (DCS), with DC referring to a patient outcome achieving pre-defined compliance or not, while DCS refers to a score anywhere from 0 (no compliance) to 10 (full compliance), calculated as the proportion of the number of drugs actually taken by an individual divided by the number of drugs prescribed for that individual over a given period of time. As our previous study of Project 686 patients with schizophrenia in Liuyang Municipality showed a 50% compliance rate, or DC of 0.5, our calculations were based on the need to detect DC in the range of 0.5 (the current rate) to 0.7 (our hypothesized improvement). In conducting our sample size analysis, we used software developed by the University of Aberdeen, U.K., specifically for clustered randomized trials [19].

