### Sample size with the binary variable drug compliance (DC)

For a cluster randomized trial, the sample size must be ‘inflated’ over that of an individual randomized controlled trial (IRCT), taking into consideration the size of the cluster as well as the intra-cluster correlation coefficient (ICC). As we are uncertain about the ICC and the effect size associated with our intervention, we did a further sensitivity analysis (as shown in Table 1) on the minimum effect size detectable in relation to various sample sizes and ICCs, assuming a 5% significance level and 80% power.

**Table 1 T1:** Sample size with binary DC

**Proportion of patients achieving DC in the control group****	**Proportion of patients achieving DC in the treatment group**	**ICC**	**Number of clusters needed***
0.5	0.6	0.01	86
		0.05	114
		0.1	148
0.5	0.7	0.01	22
		0.05	28
		0.1	36
0.5	0.8	0.01	10
		0.05	12
		0.1	16

*The exercise uses a 5% significance level at a power of 80%, with 10 patients per cluster as suggested by Project 686 registries.

**The control group proportion of patient achieving DC is based on our current research in Liuyang.

From the table above, we can see that in order to detect a minimum increase in the proportion of patients achieving DC from 0.5 to 0.6, we will need a sample of at least 860 patients, even assuming a liberal ICC of 0.01. However, if we can achieve a minimum increase of 0.5 to 0.7, even at a conservative ICC of 0.1, only 360 patients are needed for this increase to be detectable. Assuming a patient drop-out rate of 10%, we arrive at a sample size of 400 patients. Project 686 records indicate that villages in the cluster have an average of 10 patients per village; consequently, 40 villages will be needed to gather a sample of 400 villagers with schizophrenia.

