### Sample size with the continuous variable drug compliance score (DCS)

The continuous variable DCS will also be used in our data analysis. Our current research in Liuyang indicates a mean DCR score under Project 686 of 7 out of a total score of 10; for a significance level of 0.05 at a power of 80%, and a conservative ICC of 0.1, 38 villages with a total of 380 individuals will be a sample sufficient to detect an effect as small as an increase of 1 in the DCS score. Given the likelihood of drop-outs, we will include 2 additional villages for a total of 40 containing 400 individuals. Once 40 villages have been selected at random, they will be further randomized into 20 villages in the treatment group and 20 in the control group.

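### Villages are randomised, but the stated analyses make no allowance for village clustering; for t and chi-square tests of compliance the type I error is about 6% to 15.5% over the plan's own ICC range

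*Protocol article*

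**What the plan says.** On the design, the protocol article is clear. *Sampling and cluster randomized controlled design* states: "The randomization will be based on villages rather than individuals". The DCS sample size section adds, of the 40 selected villages, that "they will be further randomized into 20 villages in the treatment group and 20 in the control group".

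The sample size respects this. The DC sample size section inflates the individually randomised figure, "taking into consideration the size of the cluster as well as the intra-cluster correlation coefficient (ICC"), takes about 10 patients per village, and tabulates ICCs of 0.01, 0.05 and 0.1. Both the DC and the DCS calculations rest on 0.1, which the plan calls conservative.

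The analysis section, *Comparison between VD model and CAU model*, does not follow through. It says that "T, Chi-square and various kinds of regression tests will be used to compare DCR (binary variable), DCS (continuous variable), and hospitalization (continuous variable") and the incidence of risky behaviour. (I read DCR there as the binary DC.) Psychiatric symptoms and social function get repeated analysis of variance. The main model is a "difference-in-difference Ordinary Least Square (OLS) estimator with additional regressors to estimate population true coefficients". It is written out for the change in DCS of patient i, with one residual u_i. The same section claims greater precision for β1 than a simple difference would give. It mentions cluster randomisation only as a possible source of baseline imbalance: "it is possible (though unlikely) that all eligible individuals within a cluster could be assigned to a treatment or to a control group".

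**The concern.** Patients in one village share a village doctor, a visiting psychiatrist and local circumstances. The plan accepts that their outcomes are correlated, since it pays for this in the sample size. An analysis that then counts each patient as an independent observation understates the standard error of the programme effect. Confidence intervals are too narrow, and an ineffective programme is declared effective more often than the 5% the trial is sized for. The primary compliance outcomes are affected, and so are any secondary outcomes that vary between villages.

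The remark on whole-village allocation adds to the doubt. Under village randomisation, all eligible patients of a village are always in one arm. The plan treats as a remote possibility what its own design makes certain.

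**Working it through.** **Inputs.** Two-sided alpha 0.05 and 80% power (*Sample size*); 20 + 20 villages (DCS sample size section); m = 10 patients per village, ICC 0.01, 0.05 and 0.1, DC 0.5 against 0.7, and 10% drop-out (DC sample size section).

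**Step 1: reproduce the plan's figure.** For 0.5 against 0.7, the usual two-proportion formula without continuity correction gives 93 patients per arm. The design effect is DEFF = 1 + (m − 1) × ICC. At ICC 0.1 this is 1 + 9 × 0.1 = 1.9, so 93 × 1.9 = 176.7 per arm, or 18 villages per arm and 36 in total, as in Table 1. All nine cells of Table 1 reproduce in this way. Then 360 / 0.9 = 400 patients. The sample size is sound and assumes an analysis that allows for clustering.

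**Step 2: error rate if the analysis ignores the village.** The true standard error is √DEFF times the reported one, so the actual two-sided error is 2 × [1 − Φ(1.96 / √DEFF)].

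| m | ICC | DEFF | √DEFF | Actual error |
|---|---|---|---|---|
| 10 | 0.01 | 1.09 | 1.04 | 6.0% |
| 10 | 0.05 | 1.45 | 1.20 | 10.4% |
| 10 | 0.1 | 1.90 | 1.38 | 15.5% |
| 9 (after 10% drop-out) | 0.1 | 1.80 | 1.34 | 14.4% |

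**Step 3: check by simulation.** With 20 + 20 villages of 10 patients, ICC 0.1, no true effect and 20,000 runs, the unadjusted t test rejects in 15.4% of runs and the chi-square test in 15.8%. A t test on village means rejects in 4.7% (continuous outcome) and 5.1% (binary outcome).

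**Step 4: unequal villages.** The plan gives only an average village size. If the coefficient of variation (CV) of village size is assumed to be 0.4 to 0.8, then DEFF = 1 + [(1 + CV²) × 10 − 1] × 0.1 runs from 2.06 to 2.54, and the error at ICC 0.1 from about 17% to 22%. This is an assumption about spread, not a figure from the plan.

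**Step 5: what does not carry over.** The plan's ICCs are for DC and DCS themselves. The printed model analyses the change in DCS with covariates. Stable village differences cancel from a change; differences between villages in how much patients change do not. The ICC of the change could therefore be lower or higher than 0.1. No ICC is given for BPRS, GAF, hospitalisation or risky behaviour either, so no error rate can be computed for these.

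**The case against.** The strongest defence is that the plan never says errors are independent. OLS is a point estimator, the printed equation would look the same with village-clustered standard errors, a t test could be run on village means, and the open-ended reference to regression methods could cover a clustered model. The DCS model is offered as an example, and a journal article may leave the variance method to a fuller document.

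Part of this stands. A reader might infer that the plan commits to independent errors. The documents do not support that; what they show is that no method for village clustering is stated. But the article is not merely brief. It names the tests, prints the model with its residual and argues for the precision of β1, and clustering enters none of this.

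A reader might also infer that every analysis has an error rate of about 15%. That is not supported. The 15.5% belongs to the highest of three tabulated ICCs, one the authors call conservative while saying they are uncertain of the ICC, and to t and chi-square tests of DC and DCS.

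Finally, the sentence on whole-village allocation might be read as proof that the authors misjudge their standard errors. It concerns baseline imbalance. It contradicts the design and needs correcting, but it adds nothing to the error-rate calculation.

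**Conclusion.** The point holds: the analysis is wrong as written for a trial that randomises villages. For t and chi-square tests of DC and DCS at patient level, the type I error is about 6.0% to 15.5% over the plan's ICC range with 10 patients per village, and 14.4% at ICC 0.1 with 9. This rests on the tests being run on patients without adjustment, on equal village sizes, and on the planning ICCs applying to these outcomes. For the OLS change model, the repeated analysis of variance and the secondary outcomes, standard errors are too small wherever the relevant ICC is positive; by how much cannot be said from the document.

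**What to change.** - **DCS:** keep the difference-in-difference model, and add a village random intercept or village-clustered standard errors. With one change score per patient, either is enough.
- **DC, hospitalisation and risky behaviour:** choose one village-clustered method in advance, for example GEE with village as the cluster, or a test on village-level summaries. Fix the choice, because a logistic mixed model and GEE estimate different odds ratios.
- **Repeated BPRS and GAF scores:** use a mixed model with patient and village effects, including village-by-time, or analyse village means of change. A village intercept alone is not enough: it omits the correlation within a patient and cancels from the change contrast.
- **Throughout:** apply a small-sample correction for 40 villages (40 − 2 = 38 degrees of freedom).
- **Text:** correct the sentence that calls whole-village allocation unlikely; under the design it is certain.

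The cost is analysis wording and wider intervals. No more patients are needed on the plan's own assumptions: with 20 villages of 9 per arm, 180 / 1.8 = 100 effective patients per arm, and power for DC 0.5 against 0.7 at ICC 0.1 is about 83% (normal approximation, before the small-sample correction).

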**Methods/design:**

We will conduct a cluster randomized controlled trial in 40 villages in Liuyang, Hunan Province, China, home to approximately 400 patients with schizophrenia. Half of the villages will be randomized into the treatment group (village doctor, or VD model) wherein village doctors who have received training in a schizophrenia case management protocol will manage case records, supervise drug taking, educate patients and families on schizophrenia and its treatment, and monitor patients for signs of relapse in order to arrange prompt referral. The other 20 villages will be assigned to the control group (case as usual, or CAU model) wherein patients will be visited by psychiatrists every two months and receive free antipsychotic medications under an on-going government program, Project 686. These control patients will receive no other management or follow up from health workers. A baseline survey will be conducted before the intervention to gather data on patient’s socio-economic status, drug compliance history, and clinical and health outcome measures. Data will be re-collected 6 and 12 months into the intervention. A difference-in-difference regression model will be used to detect the program effect on drug compliance and other outcome measures. A cost-effectiveness analysis will also be conducted to compare the value of the VD model to that of the CAU group.

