### Procedures

Following a pilot study (see Section below), 40 villages (excluding the pilot study villages) will be randomly selected in Liuyang Municipality. We will conduct a baseline survey of patients with schizophrenia in the villages, collecting data on social demographics, compliance rates, clinical characteristics, and outcome measures. Researchers will explain the research to participants and obtain written informed consent from both patients and family member. And after the randomization, VDs and family members of patients will receive training and education in the 12-month case management protocol as noted in Section above. Researchers will visit VDs every month during the first three months of the study and every three months thereafter for the remaining nine months of the study, obtaining feedback and giving follow-up instructions, and recording and monitoring VDs’ case management work via questionnaire.

In the CAU model, control villages will continue to receive bimonthly visits by psychiatric professionals, who will dispense free antipsychotics per existing Project 686 protocol. No other interventions will be introduced.

Follow-up interviews will be conducted with patients in both VD and CAU model villages at 6 months and 12 months into the intervention, collecting the same data as that collected at baseline (see below).

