### Instruments

Four types of statistics will be collected at baseline and at 6 months and 12 months into the study:

Socio-demographic characteristics: age, sex, education level, marital status, work, economic status, domestic situation (living alone, with family, or with friends).

Clinical characteristics: years of illness, number of bed days in psychiatric hospital in previous two years.

Compliance: This is our primary dependent variable measure. The binary variable Drug Compliance (DC) will be recorded by interviewing patients and their family members. We define as ‘compliant’ patients who, over the past month, have taken all pills as prescribed; otherwise, patients are recorded as ‘non-compliant.’ We will report 1-month, 3-month, 6-month and 12-month compliance as the proportion of patients achieving compliance over the total number of patients. In addition, a continuous variable Drug Compliance Score (DCS) will be used to measure medication compliance. The DCS score will be measured by dividing the actual number of pills taken by the total number of pills prescribed multiplied by 10 over a given period of time, with scores ranging from 0 (complete non-compliance) to 10 (complete compliance). For example, if a patient over the past month took 20 pills out of 100 prescribed, his compliance will be (20/100) × 10 = 2 for the past month.

Clinical/outcome measures: Four types of measures will be collected.

Symptoms score: Schizophrenia is often described in terms of positive and negative (or deficit) symptoms. Negative symptoms respond less well to medication [20], particularly to the antipsychotics that are typically used for cases in our research. Therefore, we will concentrate on the positive symptoms as these correlate more strongly with medication compliance. The Brief Psychiatric Rating Scale (BPRS) will be used to evaluate positive symptoms. The BPRS is an 18-item rating scale that has been widely used in psychiatric practice and research in China, and has good to excellent reliability and validity.

Social functions: We will use the global assessment of functioning (GAF) scale, in which a score of 0 to100 is converted to a disability weight ([100-GAF score]/100). Patients with a disability weight of 0.40 or greater are classified as moderately to severely disabled.

Quality of life score: We will use the QALY weights developed by Lenert *et al*. [21].

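### Symptoms and social function have two unranked analyses; if the repeated ANOVA includes baseline and its group main effect is read, the effect is diluted by a third

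*Protocol article*

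**What the plan says.** The section on comparing the VD and CAU models gives these two outcomes their own method: "Repeated analyses of variance will be used to compare psychiatric symptoms and social function (continuous variable) scores between the two groups". It says nothing on which visits are the repeated levels, or whether the group term, the group-by-time term or a single visit decides.

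On timing, the Instruments section states: "Four types of statistics will be collected at baseline and at 6 months and 12 months into the study". The symptom and functioning scales are among those data. The Procedures section confirms two visits after the start: "Follow-up interviews will be conducted with patients in both VD and CAU model villages at 6 months and 12 months into the intervention". Baseline is therefore one of only three possible levels.

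The abstract announces another method with wider scope: "A difference-in-difference regression model will be used to detect the program effect on drug compliance and other outcome measures". The regression written out later is for the compliance score, but only as an illustration: "The example below uses DCS as the dependent variable". Its virtue, according to the article, is that it removes differences present before the programme. No such claim is made for the ANOVA.

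Compliance is the primary dependent variable. Symptom relief and social function both appear in the hypothesis.

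**The concern.** What is compared is scores, not changes, and the comparison is between the groups. In a repeated-measures ANOVA that can be read as the group main effect, which averages the arm difference over all the levels entered. If baseline is a level, one of the three differences averaged comes from before any treatment and is zero in expectation. The estimate is then pulled towards zero, and any chance imbalance among 20 villages per arm goes into it.

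The abstract's difference-in-difference model gives a second answer for the same two outcomes. If the two disagree, nothing says which one settles the hypothesis. At stake is the ability to detect a real benefit on symptoms or functioning, and a clear statement of what was tested.

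**Working it through.** **The plan's own figure.** The article gives no effect size, SD or correlation for BPRS or GAF; its sample size concerns compliance. For 0.5 v 0.7, two-sided 5%, 80% power and pooled variance under the null:

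- n per arm = [1.96√(2×0.6×0.4) + 0.84√(0.25+0.21)]² / 0.2² = 93.
- Design effect = 1 + (10−1)×0.1 = 1.9.
- 93×1.9/10 = 17.67, so 18 villages per arm, 36 in all, 360 patients; 360/0.9 = 400.

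This agrees with the article ("even at a conservative ICC of 0.1, only 360 patients are needed for this increase to be detectable") and is untouched by the present point.

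**Dilution.** Let d6 and d12 be the arm differences at months 6 and 12; the baseline difference is 0 in expectation. The three-visit main effect estimates (0 + d6 + d12)/3. The mean post-baseline effect is (d6 + d12)/2. The ratio is 2/3 whatever the pattern. Against d12:

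- sustained (d6 = d12): 2/3 = 67%
- linear (d6 = d12/2): 1.5/3 = 50%
- only at month 12 (d6 = 0): 1/3 = 33%
- waning (d6 = 1.5 d12): 2.5/3 = 83%

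**Baseline gap.** Under compound symmetry with correlation ρ, an observed chance gap b adds b(1 + 2ρ)/3 to the main effect, which is 0.67b at ρ = 0.5. A baseline-adjusted contrast removes it.

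**Power, illustrative.** Assumptions: unit SD at each visit, compound symmetry, ρ = 0.5, normal approximation, and the same design effect for every contrast. The month-12 effect is set so that a plain month-12 comparison has 80% power (non-centrality 1.96 + 0.84 = 2.80). With 180 per arm and design effect 1.9, that is 2.80×√(2×1.9/180) = 0.407 SD. The comparison between methods does not depend on the 180 or the 1.9, because both cancel.

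- Three-visit main effect: variance factor (1+2ρ)/3 = 0.667. Sustained: 2.80×0.667/√0.667 = 2.29, power Φ(0.33) = 63%. Linear: 2.80×0.5/√0.667 = 1.72, power Φ(−0.24) = 40%.
- Group-by-time, 2 df: non-centrality 2.80²×1.333 = 10.5 (sustained) or 2.80²×1 = 7.8 (linear), giving 83% or 71%.
- Change from baseline to month 12: factor 2(1−ρ) = 1, so 80%.
- ANOVA on months 6 and 12 only: factor (1+ρ)/2 = 0.75. Sustained 3.23, 90%; linear 0.75×3.23 = 2.43, 68%.
- Baseline-adjusted month 12: factor 1−ρ² = 0.75, so 2.80/√0.75 = 3.23, 90%.

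| Contrast | Sustained, ρ = 0.5 (ρ 0.3 to 0.8) | Linear, ρ = 0.5 (ρ 0.3 to 0.8) |
|---|---|---|
| Three-visit main effect | 63% (72 to 52) | 40% (48 to 32) |
| Group-by-time | 83% (69 to over 99) | 71% (55 to 98) |
| Change to month 12 | 80% (66 to 99) | 80% (66 to 99) |
| Months 6 and 12 only | 90% (94 to 84) | 68% (74 to 60) |
| Baseline-adjusted month 12 | 90% (84 to over 99) | 90% (84 to over 99) |

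**The case against.** The strongest reply is that the dilution is inferred. The sentence does not make baseline a repeated level and does not name the main effect. It fits a group-by-time test, which is not diluted, or an ANOVA on months 6 and 12 alone. That stands, and it is why the loss is stated conditionally. A reader might infer that the planned test certainly averages in baseline and shrinks the effect by a third or more; the document does not support that. Against month 12, even the third requires an effect that does not wane.

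Second, the abstract says the difference-in-difference model is the one that detects the programme effect, for other outcomes too, and the article calls its coefficient the one of most interest. A change from baseline is not diluted. This also stands, but the discussion of that coefficient is worded for the compliance score. The ANOVA sentence names symptoms and social function and is nowhere subordinated, so both methods remain.

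Third, the choice of ANOVA term for secondary outcomes is ordinarily analysis-plan detail, and a journal article is condensed. The missing term alone would not be a finding. What remains is that two methods are assigned to the same outcomes, and that one of them permits a reading with a large avoidable loss.

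Fourth, the remedy is partly preference. At a correlation of 0.8 the group-by-time test does as well as the adjusted month-12 contrast. For a sustained effect, an average of the two follow-up visits equals it at 0.5 and beats it at 0.3 (94% v 84%). That is fair; the case for the adjusted contrast is that it does well under both effect patterns and all these correlations.

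A reader might also infer an inflated false-positive rate from reading both ANOVA tests. Nothing in the article says that either test would count as success, so that charge is not made.

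**Conclusion.** The point holds in conditional form. Two unranked analyses are announced for BPRS and GAF, and the ANOVA wording leaves open a three-visit group main effect. If that is the test, it estimates exactly two thirds of the mean post-baseline effect. In the illustration its power is about 63% (sustained) or 40% (linear), against about 90% for a baseline-adjusted month-12 comparison of the same data. The 2/3 ratio needs only a baseline difference of zero in expectation. The power figures rest on assumed compound symmetry, a visit correlation of 0.5 and an 80% benchmark, none of which the article supplies for these scales.

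The weight is moderate at most. These are secondary outcomes, and the compliance analysis and sample size are unaffected. It is still worth changing, because a clearly better contrast is available from data already planned.

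**What to change.** Replace the repeated-ANOVA sentence for BPRS and GAF with one baseline-adjusted analysis that accounts for village, the unit of randomisation. One suitable form is a mixed model on the 6- and 12-month scores, with a village random effect, allowance for repeated measures within patient, the baseline score as covariate, and terms for arm, visit and arm-by-visit. Name the adjusted arm difference at month 12 as the deciding contrast and the month-6 difference as supportive. State that for these two outcomes this analysis takes precedence over the difference-in-difference model in the abstract.

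A longitudinal model that keeps baseline in the outcome vector but constrains the arms to be equal there is an acceptable equivalent.

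The cost is analysis wording only: no extra visits, data or patients. It should be settled before anyone sees results by arm.

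### The written-out DCS model analyses change without adjusting for baseline DCS, and the efficiency claimed for it does not hold against the baseline-adjusted estimator

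*Protocol article*

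**What the plan says.** The section Comparison between VD model and CAU model gives its reason for the method: "Insofar as perfect randomization and program execution are rarely achieved, we make use of an equation with a difference-in-difference" OLS estimator with extra regressors. The equation, offered as an example for DCS, has end-minus-start DCS as the outcome. Its regressors are the treatment indicator, socio-economic and demographic variables, illness severity and family care. Baseline DCS is not in the equation or in the covariate definitions. The Instruments section has compliance measured at baseline, 6 and 12 months, so the variable is available.

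The same section says that the treatment coefficient "is more efficient than other estimators as it has a smaller variance or standard error than a simple difference estimator". The sentence then adds a condition: that unobserved determinants of DCS persist over time within an individual. It also says that further regressors are included because they may determine DCS and so improve efficiency.

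**The concern.** The sentence starts from a general claim about other estimators but supports it only by comparison with the simple difference. The usual competitor in a randomized trial with a measured baseline is follow-up adjusted for baseline, and the text does not mention it. By the protocol's own reason for adding regressors, baseline DCS is an obvious candidate, and it is the one left out. At stake is the precision of the coefficient that the protocol defines as the program effect.

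**Working it through.** **Inputs from the protocol.** Two-sided 5% level, 80% power and DC 0.5 versus 0.7 (Sample size). Table 1 is computed "with 10 patients per cluster as suggested by Project 686 registries". For DCS: "a conservative ICC of 0.1, 38 villages with a total of 380 individuals", to detect a 1-point increase; 20 villages per arm.

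**Not in the protocol.** The SD of DCS and the baseline-to-follow-up correlation. Both are assumed below.

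**1. The plan's own figures.** For DC, the two-proportion formula without continuity correction gives 93 per arm. The design effect is 1 + (10 − 1) × 0.1 = 1.9. Then 93 × 1.9 / 10 = 17.67, so 18 villages per arm, 36 in all, which matches "only 360 patients are needed for this increase to be detectable". 360 / 0.9 = 400 also matches. For DCS, 38 villages follow only if the SD is about 2.45 to 2.52. For example, SD 2.5 gives 99 per arm, and 99 × 1.9 / 10 = 18.81, so 19 villages per arm. SD 2.5 is used below.

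**2. Relative variances, same correlation r within and between villages, equal SDs.** Taking the simple follow-up difference as 1, the change score has 2(1 − r) and the baseline-adjusted estimator 1 − r². Change relative to adjusted is 2(1 − r)/(1 − r²) = 2/(1 + r).

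| r | Change | Adjusted | Change / adjusted | Power: follow-up only / change / adjusted |
|---|---|---|---|---|
| 0.3 | 1.40 | 0.91 | 1.54 | 80.7% / 66.7% / 84.3% |
| 0.5 | 1.00 | 0.75 | 1.33 | 80.7% / 80.7% / 90.4% |
| 0.7 | 0.60 | 0.51 | 1.18 | 80.7% / 95.5% / 97.7% |
| 0.9 | 0.20 | 0.19 | 1.05 | 80.7% / 100% / 100% |

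Power uses 190 / 1.9 = 100 effective patients per arm, a 1-point effect and SD 2.5.

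A simulation (3,000 trials, 40 villages of 9, ICC 0.1) gave relative variances for change and adjusted of 1.44 and 0.92 at r = 0.3, 1.02 and 0.76 at 0.5, and 0.60 and 0.51 at 0.7. Mean estimates lay between 0.994 and 1.004 for a true effect of 1, so none of the estimators is biased. Adding baseline DCS to the change equation gave the same treatment coefficient as modelling follow-up DCS on baseline DCS.

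**3. Different persistence within and between villages.** Let w be the within-village and v the village-level correlation. With ICC 0.1 and 10 patients, a village mean has variance 0.10 + 0.90/10 = 0.19, and the baseline and follow-up means have covariance c = 0.10v + 0.09w. Relative to follow-up only:
- change: (2 × 0.19 − 2c) / 0.19
- adjusted, with the patient-level slope b = 0.1v + 0.9w: (0.19(1 + b²) − 2bc) / 0.19

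Example, w = 0.3 and v = 0.8: c = 0.107 and b = 0.35. Change is 0.166/0.19 = 0.87, adjusted is 0.1384/0.19 = 0.73, and the ratio is 1.20.

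| v (w = 0.3) | Change | Adjusted | Ratio | Simulated change, adjusted |
|---|---|---|---|---|
| 0.3 | 1.40 | 0.91 | 1.54 | 1.43, 0.92 |
| 0.6 | 1.08 | 0.81 | 1.34 | 1.11, 0.82 |
| 0.8 | 0.87 | 0.73 | 1.20 | 0.86, 0.74 |
| 1.0 | 0.66 | 0.64 | 1.03 | 0.64, 0.63 |

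**4. Can change win?** The variance is quadratic in the slope, with its minimum at b* = c/0.19. Change uses slope 1, so adjustment loses only if |b* − b| exceeds 1 − b*. Here b* − b = 0.426(v − w), and 1 − b* = 0.526(1 − v) + 0.474(1 − w). For v and w between 0 and 1, |v − w| is at most the larger of 1 − v and 1 − w, so the first quantity never exceeds the second. At the planning ICC and village size, with equal SDs, adjustment is never worse (ignoring the small cost of estimating the slope).

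**The case against.** The efficiency claim is conditional. Under strong persistence a change score does beat a simple follow-up difference, which is the standard case for difference-in-difference. That stands, so the sentence cannot be called plainly false. What fails is its wider opening about other estimators.

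Four stronger readings are tempting, and the documents do not support them:
- *Change is worse than ignoring baseline whenever the patient-level correlation is below 0.5.* This needs equal correlation within and between villages. At w = 0.3 and v = 0.8 the overall patient-level correlation is 0.35, yet change has about 13% less variance than the follow-up difference. The 40% excess at r = 0.3 is one scenario, not a general result.
- *The estimate is biased because change over-corrects a chance baseline imbalance.* That describes a single imbalanced allocation. Over randomizations the estimator is unbiased.
- *Many patients start at the ceiling, so change is the wrong outcome.* A patient at 10 cannot exceed 10 at follow-up under either model, so the ceiling does not separate the two.
- *The same defect affects DC, BPRS and GAF.* The variance argument is for continuous DCS, and the protocol assigns symptoms and social function to repeated analyses of variance.

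It is also fair that the equation is called an example, that its covariates may recover some precision, and that covariate lists are often settled in an analysis plan. But it is the only model written out, it defines the program effect, and the efficiency statement is made here.

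**Conclusion.** The point holds as a matter of precision for the DCS model. The statement about other estimators holds at most against the simple follow-up difference under strong persistence, and not against the baseline-adjusted estimator. With equal SDs and one common correlation, omitting baseline DCS inflates the variance by 1.54, 1.33 and 1.18 at r = 0.3, 0.5 and 0.7. With w = 0.3, the ratio falls to about 1.2 at village correlation 0.8 and to nearly 1 at 1.0. The correlations are assumptions shown as a range, and the power figures also rest on an SD of 2.5 inferred from the 38 villages. The gain may be large or small, but adjustment was at least as precise in every scenario examined.

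**What to change.** Add baseline DCS as a regressor in the DCS equation, and account for village clustering in the model or its standard errors. Whether the outcome is then written as change or as follow-up DCS makes no difference to the treatment coefficient. Keep the change-score model without baseline DCS as a sensitivity analysis. Reword the efficiency sentence so that it claims an advantage only over a simple follow-up difference, and only when DCS persists strongly over time.

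The cost is one model term and one sentence. Baseline DCS is already collected, and the sample size does not change.
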